### Blinding

Investigators will be masked to group allocation, but participants and research staff will not, given their active study roles.

### Usual care

Standard of care for LTBI patients at this clinic includes an initial discussion of medication risks, benefits, and side effects. Treatment usually involves daily self-administration of medication for a prolonged period of therapy. Treatment typically involves taking rifampin 600 mg daily for 4 months or isoniazid 300 mg daily for 9 months. If a patient agrees to treatment, they are given a 30-day supply of medication. Subsequent follow-up involves monthly clinic visits, at which time there is an assessment of symptoms, side effects, and adherence; blood-work is performed; and another month’s supply of medication is provided. The usual practice of care with regard to adherence is a phone reminder prior to the next appointment.

### Intervention

Text group participants will receive a daily text reminder sent by an automatic messaging system in addition to the standard of care. This automation will anonymize messaging to all but the study coordinator, who sends out the message. Participants will be asked optimal times to receive daily texts and will receive texts in their language of choice. Participants’ phone numbers will be entered into a secured web platform to automatically send text message reminders at pre-specified intervals. A delivery report function will be used to verify that messages were received and opened. The system meets the key requirements of a highly functional texting system, including customization, personalization, message notification, and remote access [42]. The script sent to individuals will state “This is a reminder to take your medication. Please respond.” The Platform for Research Integrated Messaging (PRiM), a web-based software suite developed at the University of Arizona, allows text messaging integration and management of text messages. It is hosted on secure servers, includes only de-identified data and delivered as SaaS (Software as a Service). To the user, text messages appear to come from a specific and established phone number. Participants will use existing mobile phone services; while phones and network airtime will not be paid for, participants will be provided a $40 incentive, paid at the 2-month visit and at final survey completion. Participants can request to opt out of the intervention at any time by calling or texting “stop.”

### Outcome measures

All outcomes will be assessed through in-person participant visits or collection from clinic records. Questionnaires will be completed by trained interviewers who are blinded to participant allocation.

The primary feasibility outcomes are summarized in Table 1.

**Table 1 Tab1:** Feasibility outcomes

Outcome	How assessed	Target
Recruitment	How many approached by clinic, how many referred, how many study eligible, how many consented; why ineligible or refused; how long to recruit each patient	40% recruitment rate, based on recruitment of all eligible
Retention	How many drop out at each monthly time point, who and why	70% retention rate
Patient satisfaction and acceptability	Patient perceptions, satisfaction, and acceptance of the intervention through pre- and post-surveys	75% satisfaction rate based on positive responses to questionnaires

While this pilot study will not have the power to detect differences in efficacy, efficacy outcomes will be measured to test procedures for early indication of a promising intervention. The primary efficacy outcome is the difference in proportion of participants completing treatment in each of the study groups. Successful treatment completion is defined as taking at least 80% of the doses of rifampin prescribed within 20 weeks [43]. Estimates of treatment completion will be used to indicate whether the treatment appears promising and to estimate sample size for a future definitive trial. Additional secondary outcomes include proportion of missed visits out of total scheduled visits; the number and length of delays in medication refill; number of missed doses; overall length of treatment (time to dropout); and self-reported adherence. While potentially overestimating true adherence, self-reported adherence is a robust measure of adherence [44, 45]. A brief pre-survey and more detailed semi-structured interviews will be conducted with all individuals to qualitatively assess preferences, attitudes, and satisfaction with the study, as well as barriers to adherence.

The following assessments will be completed by participants (Fig. 1), as per the SPIRIT Statement [46].

**Fig. 1 Fig1:**
[figure not shown]
Schedule of enrolment, interventions, and assessments

### Sample size

The sample size of 40 will yield a 5% margin of error (95% confidence interval half-width) of no greater than 7.7%, for any of the binary feasibility outcomes (recruitment, retention), using the formula $$ p\pm 1.96\sqrt{\frac{p\left(1- p\right)}{n}} $$ for a single binary proportion and the value of *p* which maximizes the standard error (*p* = 0.5). A sample size of *n* = 40 participants [47] is expected to provide data sufficient to estimate variability in outcome measures as well as to assess trial feasibility. Furthermore, Whitehead et al. have shown that 40 participants in a pilot study are optimal when the future main trial is expecting a small to medium effect size [48]. We also expect qualitative data to be saturated with 30 interviews, at which we expect to yield sufficient data to achieve redundancy. However, we will increase the sample size until saturation is reached if needed [49].

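### The stated 95% half-width of at most 7.7% with n = 40 is about half what the protocol's own formula gives (15.5%), and recruitment is not measured on n = 40

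*Protocol article*

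**What the plan says.** The Sample size section of the protocol article opens with a precision statement: "The sample size of 40 will yield a 5% margin of error (95% confidence interval half-width) of no greater than 7.7" per cent. Its scope follows at once: "of no greater than 7.7%, for any of the binary feasibility outcomes (recruitment, retention"). The formula is printed as p ± 1.96·sqrt(p(1−p)/n), "for a single binary proportion and the value of *p* which maximizes the standard error (*p* = 0.5").

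The section supports 40 in two further ways, neither with a calculation: a cited publication on pilot trial size, and an expectation that 30 interviews will saturate the qualitative data.

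Table 1 under Outcome measures sets the targets for the primary feasibility outcomes:
- recruitment: "40% recruitment rate, based on recruitment of all eligible"
- retention: "70% retention rate"
- satisfaction and acceptability: "75% satisfaction rate based on positive responses to questionnaires"

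**The concern.** The sentence gives every input to its own calculation (n, p, the multiplier and the formula), so the result can be checked without outside information. The printed result does not follow from them.

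The feasibility proportions are the primary outcomes, and the Study objectives section says the data will be used to design a definitive trial. The width of the interval around each proportion is therefore much of what this pilot has to offer. If the printed margin is believed, a retention rate seen at the target would look clearly better than 60% when it is not, and attrition in the main trial could be planned too optimistically.

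A second problem sits in the same sentence. One bound at n = 40 is given for both recruitment and retention, but Table 1 measures recruitment among all eligible patients, and 40 is the number who enrol.

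**Working it through.** **Inputs.** From Sample size: n = 40, p = 0.5, multiplier 1.96, stated half-width no greater than 7.7%. From Table 1: targets of 40% (recruitment, of all eligible), 70% (retention) and 75% (satisfaction). From Overview: 1:1 allocation, so about 20 per arm.

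**1. The plan's own figure.**
1.96 × sqrt(0.5 × 0.5 / 40) = 1.96 × 0.07906 = 0.1550, or 15.5%. The printed 7.7% is not reproduced.

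Half of 15.495% is 7.75%. The same value results if p(1−p) is left outside the square root: 1.96 × 0.25 / sqrt(40) = 0.0775. That slip is a plausible cause, but it is an inference.

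**2. Does another convention give 7.7%?** At n = 40 and p = 0.5:

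| Variant | Half-width |
|---|---|
| 90% two-sided (or 95% one-sided) | 13.0% |
| 80% two-sided | 10.1% |
| One standard error | 7.9% |
| Wilson 95% | 14.8% |
| Clopper-Pearson 95% | 16.2% |
| Continuity-corrected 95% | 16.7% |
| Finite-population correction, N = 100 | 12.1% |

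None does. The full interval width would be 31%, so a mix-up of full and half width does not explain it either.

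**3. What 7.7% would require.**
- At p = 0.5: n = 0.25 × (1.96 / 0.077)² = 161.98, about 162.
- At n = 40: p of about 0.066 or 0.934. The section specifies 0.5.

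**4. Retention (denominator 40).**
- Worst case: 15.5%.
- At the 70% target: 1.96 × sqrt(0.7 × 0.3 / 40) = 14.2%.
- If 28 of 40 are retained, the protocol's formula gives 70% ± 14.2%, or about 56% to 84%. The printed margin would suggest 70% ± 7.7%, or about 62% to 78%.

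**5. Recruitment (denominator N eligible).** With 40 enrolled and recruitment rate p, N = 40/p. The half-width becomes 1.96 × sqrt(p(1−p)/N) = 1.96 × sqrt(p²(1−p)/40).
- At the target, p = 0.4 and N = 100: 1.96 × sqrt(0.24/100) = 9.6%.
- At p = 0.5, N = 80: 1.96 × sqrt(0.25/80) = 11.0%.
- The expression p²(1−p) is largest at p = 2/3, so N = 60: 1.96 × sqrt(0.2222/60) = 11.9%.

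So 7.7% is not an upper bound for recruitment either. The discrepancy is smaller there: 9.6/7.7 is about 1.2 at the target, and 11.9/7.7 about 1.5 at worst.

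**6. Satisfaction, for reference only.** At the 75% target:
- if all 40 respond: 1.96 × sqrt(0.75 × 0.25 / 40) = 13.4%
- if only about 20 text-arm participants do: 1.96 × sqrt(0.75 × 0.25 / 20) = 19.0%

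**The case against.** The arithmetic is not open to dispute, but four further conclusions might be drawn from it that the protocol does not support.

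**That 40 is an unsupported sample size.** The pilot-size citation and the saturation argument do not depend on the 7.7%. It is the only calculation shown, but its failure leaves the other two supports where they were.

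**That the misstatement covers all three feasibility outcomes, with satisfaction resting on 20 people.** The bound is stated for recruitment and retention only. Table 1 does mention acceptance of the intervention, which makes a text-arm denominator plausible. Against that, the Outcome measures and Data collection sections have all participants interviewed, and attitudes are assessed to both texting and phone reminders. The denominator is not settled by the text, so any satisfaction figure rests on an assumption.

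**That precision is overstated twofold throughout.** This holds for the printed calculation and for retention's worst case. It does not hold for recruitment on its own denominator.

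**That a formal decision will go wrong.** The protocol article ties no stopping or progression rule to the 7.7%. Statistical methods describes the feasibility analyses as mainly descriptive, and the Discussion advises cautious interpretation. The effect is on interpretation and planning.

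The 5% margin-of-error wording can also be read charitably, as the 5% error level that goes with a 95% interval. It is loose wording and need not be a contradiction.

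All of these limits stand. None of them makes 7.7% the result of the stated formula.

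**Conclusion.** The precision statement is wrong as written. The protocol's own inputs give a worst-case 95% half-width of 15.5%, about twice the 7.7% printed, and this needs no outside assumption. For retention the correct figures are at most 15.5%, and 14.2% at the 70% target, taking all 40 participants as the denominator.

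Recruitment should not have been given a bound at n = 40 at all. On the eligible population it is about 9.6% if the 40% target is met exactly, and no more than about 11.9% at any rate, provided 40 enrol.

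The finding concerns the claimed precision alone. It should be corrected because it misstates, in the favourable direction, what the pilot can say about two of its primary outcomes, and the correction is cheap.

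**What to change.** Keep n = 40 and revise the opening of the Sample size section:

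- Replace the 7.7% bound with a 95% half-width of at most 15.5% for retention (14.2% at the 70% target).
- State recruitment precision separately, on the number eligible: about 9.6% if 40 of 100 eligible patients enrol, and no more than about 11.9% for any recruitment rate when 40 enrol.
- Remove the 5% margin-of-error wording, or say that it means the error level of the 95% interval.
- If a satisfaction figure is added, state its denominator as an assumption: 13.4% at the 75% target if all 40 respond, 19.0% if only about 20 text-arm participants do.
- Report each feasibility rate with its 95% confidence interval beside its target. The choice of interval method can be left to the analysis plan.

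The cost is one rewritten paragraph and a less favourable stated precision. Sample size, procedures and planned group comparisons do not change.

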### Data collection, management, and analysis

Trained interviewers will collect socio-demographic information and clinical data through in-person participant visits or collection from clinic records for all participants, including adherence rates (dose counts, appointments) at baseline and then on a monthly basis. Additionally, information will be collected at baseline regarding sharing of phones, baseline perceptions of texting, and frequency of texting. Per usual care, participants are expected to return to clinic once a month for a check-in and medication refill. Self-reported missed doses and pill bottle counts are recorded in the medical chart and will be abstracted to a study monitoring log. Figure 1 shows the various data elements collected at study time points and Fig. 2 a sample visit protocol for the 4-month regimen.

**Fig. 2 Fig2:**
[figure not shown]
Sample visit protocol, 4-month regimen

Participants will be prospectively followed until treatment completion or dropout. We will define participants as lost to follow-up if they are unable to be traced per clinic protocol (two phone calls and a certified letter). The research coordinator will maintain a log documenting refusals and reporting recruitment numbers.

Detailed semi-structured interviews will be conducted with all individuals during their final visit to qualitatively assess preferences, attitudes, and satisfaction with the study intervention. User attitudes will be assessed for both the texting intervention and phone reminder system. Text group participants will be asked for reasons for non-response. These might include forgetting to text back, being too busy, personal reasons, or not understanding the protocol. Treatment defaulters, as assessed through chart review, will be asked for non-adherence reasons and satisfaction with various reminder systems through a one-time phone interview. All interview guides will have been piloted during staff training and presented by an interviewer familiar with the language or else with the aid of an interpreter service. Participants will be asked whether messages are useful and acceptable, whether they found the message text and format to work, and are of preferred quantity, frequency, and timing of use. Information will also be collected to better understand initial expectations and whether attitudes had changed towards the intervention throughout the process. In addition, they will be asked whether they would like to keep using the text message reminders after the study and whether they would recommend the text message reminder system to others. We anticipate including some redundancy of questions to assess internal consistency of responses. We will also collect (a) demographic characteristics of participants, (b) perceived benefits of, and barriers to, LTBI treatment completion, (c) self-efficacy to complete treatment, (d) perceived susceptibility to TB disease, (e) satisfaction with provider interactions and patient education, and (f) preferred reminder system, including whether phone sharing might have affected the intervention and perceptions of costs.

Study data will be collected and managed using REDCap (Research Electronic Data Capture) electronic data capture tools hosted at the University of Arizona’s College of Medicine. REDCap is a secure, web-based application designed to support data capture for research studies, providing (1) an intuitive interface for validated data entry; (2) audit trails for tracking data manipulation and export procedures; (3) automated export procedures for seamless data downloads to common statistical packages; and (4) procedures for importing data from external sources. All data will be password-protected and de-identified [50]. Data will be entered at the time of collection, and clinic data will be abstracted by the clinic coordinator and integrated into the database. To facilitate analysis, the database will include the ability to generate custom reports exportable to other applications. Summary reporting of data will be conducted monthly to ensure satisfactory data quality. Regular meetings will be held with co-principal investigators to assess progress of data collection.

The database will also be used to capture lack of response and number of approach attempts. Individual response rates will be calculated as the number of user responses divided by the total number of surveys sent out. All data will be kept on secured servers. Questionnaires will be administered in confidentiality and responses kept in a secured office.

### Statistical methods

Analyses regarding feasibility of the study will primarily be descriptive in terms of recruitment and retention rate, reasons for dropout, and deviations from protocol. Participation bias will be assessed by comparing individuals included in the study to study refusals as well as broader clinic participant characteristics.

Qualitative data will be transcribed and analyzed for patterns and themes using NVivo 10, a qualitative analysis program with which a member of the team has substantial experience [51, 52]. Answers to open-ended questions regarding barriers and benefits of the reminder systems will be categorized and described.

We will compare the proportion of participants completing treatment in each of the study groups in order to assess preliminary efficacy [43]. Results will be reported as the number (%) of participants for each treatment group, the risk difference, and 95% confidence intervals. Secondary outcomes will include proportion of missed visits out of total scheduled visits; the number and length of delays in medication refill; number of missed doses; overall length of treatment (time to dropout); and self-reported adherence.

Rescheduled or canceled appointments will not be considered as missed although rate of canceled or rescheduled appointments will be collected. Comparisons of the intervention group with the control group for all continuous or count outcomes will be carried out using *t* tests. Proportions will be compared using a non-continuity-corrected test of proportions. Time to dropout will be described using survival analysis methods.

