### Participants

Forty participants from PCHD are being recruited, with adequate representation expected from samples previously noted to fail treatment [13]. Pima County Health Department prioritizes LTBI screening based on recent contact to an infectious TB patient, migration from a high-burden TB country, as well as the USPSTF guidelines [9]. Persons who are at least 18 years of age and able to provide informed consent, agree to initiate LTBI treatment, are prescribed self-administered 4-month rifampin or 9-month isoniazid therapy, and have a phone that can receive text messages, will be eligible for the study. Participants will also need to be able to communicate via text messaging or have a family member or friend able to provide assistance with messages for the duration of the study. Patients are ineligible if they currently have active tuberculosis disease. Participants from the pilot will not be included in a proposed larger follow-up study.

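### Missed doses and refill delays are compared as raw counts although follow-up ends at dropout; unless doses after dropout are counted, an early defaulter can score better than a completer

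*Protocol article*

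**What the plan says.** All references are to the protocol article.

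- **Outcomes.** Statistical methods lists, among the secondary outcomes, "the number and length of delays in medication refill; number of missed doses", with no denominator. The same list gives missed visits one: "proportion of missed visits out of total scheduled visits".
- **Tests.** "Comparisons of the intervention group with the control group for all continuous or count outcomes will be carried out using" t tests. For the rest, "Proportions will be compared using a non-continuity-corrected test of proportions". The unit of analysis for missed visits is not named.
- **Follow-up.** Data collection, management, and analysis (text after Fig. 2): "Participants will be prospectively followed until treatment completion or dropout".
- **Source of missed doses.** Same section: "Self-reported missed doses and pill bottle counts are recorded in the medical chart", from where they are abstracted to a study log.
- **Course length.** Eligible patients "are prescribed self-administered 4-month rifampin or 9-month isoniazid therapy" (Participants). Under Usual care, "they are given a 30-day supply of medication" at the start and resupplied at monthly visits.

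No rule is given for doses after dropout, and no rate, offset or allowance for regimen is mentioned for the counts.

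**The concern.** A count of missed doses measures adherence only if everyone is observed over a comparable number of doses. Here the number at risk ends at dropout and depends on the regimen. If the chart stops recording misses when a patient stops attending, someone who quits after the first month has few recorded misses, although most of the course was never taken. An intervention that keeps patients on treatment then lengthens the period over which its arm can accrue misses, and the comparison works against it.

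Refill delays have the same weakness. With 30-day supplies, a 4-month course has 4 - 1 = 3 refills that can be late and a 9-month course has 9 - 1 = 8. A patient who never returns after the first supply may have none, depending on how non-return is coded.

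Missed visits already have a denominator. The question there is whether visits are pooled over participants, which would treat repeated visits by one person as independent.

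What is at stake is the choice of outcomes for the definitive trial: Study objectives names fewer missed appointments and doses among the hypotheses that trial will test.

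**Working it through.** The article gives no figure for these outcomes, so there is none to reproduce.

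**Inputs from the article.** 40 participants at 1:1, so 20 per arm. Daily dosing for 4 or 9 months; with 30-day months, 4 × 30 = 120 or 9 × 30 = 270 doses. US completion of 39-65% (Background), midpoint 52%, hence 48% dropout.

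**Assumptions not in the article.** On-treatment miss rate 10% unless stated; text-arm dropout 33%; dropout uniform over the course; no misses recorded after dropout; ICC 0.1-0.3 for missed visits.

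**1. Single patients.** A patient who quits after month 1, having missed 25% of doses, scores 0.25 × 30 = 7.5. A completer who misses 10% scores 0.10 × 120 = 12 or 0.10 × 270 = 27. The defaulter has the lowest count.

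**2. Arm means, 120-dose course.** A completer misses 12 doses. A defaulter takes part for 60 doses on average and misses 6; counted over the planned course this is 6 + 60 = 66.

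| | Control (48% dropout) | Text (33% dropout) |
|---|---|---|
| Mean doses at risk | 0.52×120 + 0.48×60 = 91.2 | 0.67×120 + 0.33×60 = 100.2 |
| Raw missed doses | 0.52×12 + 0.48×6 = 9.12 | 0.67×12 + 0.33×6 = 10.02 |
| Not taken, planned course | 0.52×12 + 0.48×66 = 37.92 | 0.67×12 + 0.33×66 = 29.82 |

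The raw count makes text look worse by 0.9 dose. The planned-course measure shows text better by 8.1 doses (31.6% against 24.9% of 120).

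**3. How firm is the reversal?** The raw means are equal when the text arm misses 9.12 / 100.2 = 9.1% of doses. At 8% its mean is 0.08 × 100.2 = 8.0, the right direction.

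**4. Simulation, 20 per arm.** Half on each regimen, completion 39% control against 65% text, miss rates varying between patients.

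| On-treatment miss rate | Raw count, text minus control | Share of prescribed doses not taken |
|---|---|---|
| 10% in everyone | +2.6 doses; text looks worse in 66% of trials | -12 points |
| 10% completers, 20% defaulters | about 0 | -13 points |

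Over a rifampin share of 25-100%, the raw difference runs from +1.6 to +3.2 in the first row and from -0.3 to +0.2 in the second. With no effect on dropout or dose-taking, the t test on raw counts rejects in 4-5% of trials, so its type I error is sound.

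**5. Regimen.** Randomisation balances regimens in expectation, so there is no bias. By chance, with half on each regimen, the arms differ by 4 or more isoniazid patients in about 27% of trials. Four extra completers on isoniazid shift an arm mean by 4/20 × (27 - 12) = 3 doses at equal adherence. That is noise.

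**6. Missed visits, only if pooled.** Design effect = 1 + (m - 1) × ICC; type I error = 2 × [1 - Φ(1.96 / √design effect)].

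| Visits per person | ICC 0.2 | ICC 0.3 |
|---|---|---|
| 4 | design effect 1.6, 12% | design effect 1.9, 15% |
| 9 | design effect 2.6, 22% | design effect 3.4, 29% |

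The second row needs everyone on 9 months with no dropout. A simulation with mixed regimens (rifampin share 25-75%), 52% completion and 15% of visits missed gave 10-12%, 15-19% and 20-25% at ICC 0.1, 0.2 and 0.3. One proportion per participant, compared by t test, stayed at 4-5%.

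**The case against.** Much can be said for the plan.

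- **The rule after dropout is not written.** Nothing says that undelivered doses are excluded from missed doses, and a fuller plan may settle this. That stands, and makes the dropout argument conditional. But the text as published gives a bare number, follow-up that ends at dropout and chart-recorded misses, and these point to not counting them.
- **The wrong direction is fragile.** It assumes that a daily reminder leaves daily dose-taking unchanged and acts only on dropout. The 0.9-dose reversal is also smaller than its sampling SD of about 1.5 doses with 20 per arm and binomial misses only. This stands. A reader might infer that the raw count will show a working intervention as harmful; the documents do not support that. What remains is that the count understates any benefit that comes through retention.
- **The visit-level test is inferred.** The test of proportions plainly fits treatment completion, and a missed-visit proportion per participant could go to the t test. This stands. A reader might infer that the plan commits to pooled visits and so to type I error of 20% or more; it does not name the unit.
- **Default is captured elsewhere.** Completion is to be compared between arms, and time to dropout is described by survival methods. A reader might think that these counts decide whether the intervention is promising. Outcome measures gives that role to treatment completion and disclaims power for efficacy.

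**Conclusion.** The point holds in a limited form. Followed as written, the comparison of missed doses and refill delays mixes adherence with time under observation. If doses after dropout go uncounted, a benefit through retention can disappear or slightly reverse: 9.1 against 10.0 missed doses under the assumed dropout and equal 10% miss rates, with no reversal once the text arm misses about 9.1% or less. The fault lies in what is estimated, not in the error rate of the t test. Unequal course lengths make the counts noisier but do not bias them.

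The missed-visit part is conditional on pooling. If visits are pooled, type I error is about 12-15% with 4 visits each at an assumed ICC of 0.2-0.3, and higher with more visits.

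The importance is moderate. These are secondary outcomes of an unpowered pilot, and they bear on which adherence measures the definitive trial takes forward.

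**What to change.** Define one value per participant for each outcome.

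1. **Missed doses:** percent of the planned course not taken, with doses after discontinuation counted as missed. Report the on-treatment miss rate alongside.
2. **Refill delays:** number per month on treatment.
3. **Missed visits:** each participant's proportion of scheduled visits missed, compared by t test or by a model clustered on participant. State whether visits after dropout remain in the denominator.
4. **Regimen:** present these outcomes by regimen or adjust for it.

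The cost is a few sentences in the analysis section and a few lines of code, with no new data. The one drawback is that the planned-course measure overlaps with treatment completion, which is why the on-treatment rate should be shown with it.

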**Methods/design:**

We aim to determine the feasibility and acceptability of text reminders for improving adherence in latent TB patients using a randomized controlled single-blinded trial, measuring adherence through an increase in treatment completion rates. Forty adult LTBI participants will be randomized to either text messages plus phone call reminders or phone call reminders only (usual care). Recruitment, retention, and study acceptability will be assessed as primary outcomes.

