## Methods/design

### Overview

This is a single-blinded randomized controlled parallel trial to test the feasibility of using text messages to improve LTBI treatment adherence. Randomization will be performed with a 1:1 allocation. The project is funded through the American Lung Association and is being led by researchers at the University of Arizona with recruitment and collaboration taking place at the Pima County Health Department (PCHD) TB Control Program in Tucson, AZ, USA. This manuscript adheres to the SPIRIT checklist reporting guidelines (Additional file 1).

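### Five secondary outcomes are assigned only significance tests, in a pilot that disclaims power for efficacy; estimates with 95% intervals should be the stated method

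*Protocol article*

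**What the plan says.** The Outcome measures section concedes a limit: "While this pilot study will not have the power to detect differences in efficacy". It therefore sets a modest purpose for the efficacy data, namely to try out the procedures and look for early signs of promise. The Study objectives section adds that the data will be used to design a definitive trial. The Sample size section gives estimating the variability of outcome measures as one reason for choosing 40 participants.

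The Statistical methods section then treats the efficacy outcomes in three ways.

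- **Treatment completion** (primary efficacy outcome): "Results will be reported as the number (%) of participants for each treatment group, the risk difference, and 95% confidence intervals".
- **Continuous, count and proportion outcomes:** "Comparisons of the intervention group with the control group for all continuous or count outcomes will be carried out using" *t* tests, and "Proportions will be compared using a non-continuity-corrected test of proportions". The list they apply to begins: "Secondary outcomes will include proportion of missed visits out of total scheduled visits; the number and length of delays in medication refill". It continues with missed doses, length of treatment (defined as time to dropout) and self-reported adherence.
- **Time to dropout:** described by survival methods, with no test named.

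No significance level, multiplicity rule or exploratory label is attached to the tests.

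**The concern.** For completion, the stated method fits the stated purpose: an estimate and its uncertainty. For five secondary outcomes, the article names a hypothesis test and no estimate or interval. A test answers whether the arms differ, which the protocol says this study is too small to answer.

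The people planning the definitive trial need something else from these outcomes: a standard deviation, a plausible range for the difference, and a view of which measures behave well. A p-value gives none of these. At this size a non-significant result is expected even if the intervention works, and a significant one will usually overstate the effect. The outcomes matter because the Study objectives section names self-reported adherence, missed appointments and missed doses among those the definitive trial will examine.

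**Working it through.** **The plan's own figure.** The protocol states no power, significance level or familywise error rate for efficacy, so there is no figure of this kind to reproduce. Its one precision figure, a 7.7% half-width in the Sample size section, concerns the feasibility proportions. The formula given there yields 1.96 × √(0.25/40) = 15.5%. That is a separate matter and does not enter the calculations below.

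**Inputs**
- 40 participants (Abstract) and "Randomization will be performed with a 1:1 allocation" (Overview): 20 per arm.
- 70% retention target (Table 1): 0.7 × 20 = 14 per arm.
- Effect size: the Sample size section expects a small to medium effect in the main trial but gives no number. Assumed here: standardized difference d = 0.2 to 0.5.
- Significance level: not stated for the tests. Assumed two-sided 5%, in line with the 95% intervals.

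**Step 1: count the tests.** Six secondary outcomes are listed: missed-visit proportion, number of refill delays, length of refill delays, missed doses, length of treatment (time to dropout) and self-reported adherence. Time to dropout is described and not tested, which leaves five. Adding the test of proportions for completion makes six.

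**Step 2: chance of at least one false positive,** 1 − 0.95^k if independent, and by simulation with equal correlation between the test statistics:

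| Tests | Independent | Correlation 0.3 | Correlation 0.7 |
|---|---|---|---|
| 5 | 22.6% | 20.9% | 14.9% |
| 6 | 26.5% | 24.2% | 16.4% |

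The correlated columns are more realistic. Medication is handed out at monthly visits, so a missed visit tends to bring a refill delay and missed doses.

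**Step 3: what a *t* test needs to reach significance.** The smallest significant observed d is t(0.975, 2n − 2) × √(2/n).
- 20 per arm: 2.024 × √(2/20) = 0.64.
- 14 per arm: 2.056 × √(2/14) = 0.78.

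Both exceed the top of the assumed range of 0.2 to 0.5. If the true effect lies in that range, every significant result must overstate it or have the wrong sign.

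**Step 4: power and average exaggeration.** These come from 400,000 simulated two-sample *t* tests per scenario. Exaggeration is the mean absolute estimate among significant results, divided by the true difference.

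| True d | Power, 20 per arm | Exaggeration, 20 per arm | Exaggeration, 14 per arm |
|---|---|---|---|
| 0.2 | 9.5% | 3.8-fold | 4.4-fold |
| 0.3 | 15% | 2.6-fold | 3.0-fold |
| 0.4 | 23.5% | 2.0-fold | 2.3-fold |
| 0.5 | 34% | 1.7-fold | 1.9-fold |

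The uncorrected test of two proportions behaves similarly at 20 per arm: 50% against 65% gives power of 15% and 2.6-fold exaggeration, and 50% against 70% gives 24% and 2.0-fold. These rates are illustrative assumptions.

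**The case against.** The strongest reply is that little depends on these tests. The feasibility targets in Table 1 are recruitment, retention and satisfaction. The Outcome measures section uses estimates of completion, not a p-value, to judge promise and size the next trial. Exaggeration arises when results are selected on significance, and the protocol has no such rule. The Discussion asks for cautious interpretation. A journal article also condenses: nothing in it excludes intervals for secondary outcomes, and multiplicity in a pilot is commonly left to a fuller plan.

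Most of this stands, and it keeps the point minor. The absence of a multiplicity adjustment is not itself a defect in a pilot. What remains is that the article is not silent on secondary comparisons. It names a method, that method is a test, and it contrasts with the estimate and interval given for completion a few sentences earlier.

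A reader might go further and infer three things that the documents do not support.

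- **That every efficacy outcome is only tested, with about a 30% chance of a false positive.** That figure needs seven independent tests (1 − 0.95^7 = 30.2%). Reaching seven means counting time to dropout, for which no test is named, and completion, which already has an estimate and interval.
- **That any significant effect will be inflated about 2.5-fold.** That value follows from an assumed 15-point gain in completion (52% against 67%: power 15.5%, 2.55-fold). It is not a result for any secondary outcome, and the protocol gives no such gain.
- **That p-values must be removed.** That is a preference in pilot reporting, and other conventions are defensible.

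**Conclusion.** The point holds in a limited form. For five secondary outcomes the article names only significance tests, although it disclaims power for efficacy and wants the data for designing the next trial and estimating variability.

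At an assumed two-sided 5%, the chance of at least one false positive is about 23% for five independent tests and 26% for six, or roughly 15–24% with correlations of 0.3 to 0.7. Over an assumed d of 0.2 to 0.5 with 20 per arm, power is about 10–34% and exaggeration about 3.8- to 1.7-fold. It is somewhat worse, 4.4- to 1.9-fold, if retention only meets its 70% target. The effect sizes, significance level and correlations are all assumptions.

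No stated decision rests on a secondary p-value, so this is a minor improvement and does not threaten the study's feasibility aims.

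**What to change.** Amend the two test sentences in the Statistical methods section; do not simply delete them, since they carry the only stated method for these comparisons. Suggested text:

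> Each between-arm secondary outcome will be reported as an estimated difference with a 95% confidence interval, together with the standard deviation in each arm where the outcome is continuous. Any p-values are exploratory, and no conclusion about efficacy will be drawn from them.

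The description of time to dropout by survival methods and the reporting of completion can stay as they are. The change needs no extra data or participants. It costs a little more reporting and puts less emphasis on p-values.
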